# 0 reading represents “no pain”

# 3 readings represent “mild pain”

# 4- 6 readings represent “moderate pain”

# 7- 10 readings represent “severe pain”

- **Secondary Outcomes:**

The quantitative limulus amoebocyte lysate (LAL) test was used to measure endotoxin concentrations in the root canals by a commercial standard kit. The LAL assay is highly sensitive for detection of minute concentrations of endotoxin. LAL is an aqueous extract of blood cells (amoebocytes) from the horseshoe crab, Limulus polyphemus, that reacts with bacterial endotoxin or LPS. This reaction is the basis of the LAL test, which is used for the detection and quantification of bacterial endotoxins.

- **Participant timeline:**

1. Patients will be selected from the clinic of endodontic after eligibility.
2. They will be randomized and pretreatment diagnosed and radiographed at the same visit of treatment.
3. Patients will be treated in two visits and will record preoperative and postoperative degree of pain at 6, 12, 24 and 48hrs.
4. Patients will return pain charts to the operator on the second visit.

| **periods** | **Recruitment** | **Diagnosis** | **Periapical radiograph** | **Randomization** | **Follow up for postoperative pain** |
| --- | --- | --- | --- | --- | --- |
| Zero |  |  |  |  |  |
| 6 h |  |  |  |  |  |
| 12 h |  |  |  |  |  |
| 24 h |  |  |  |  |  |
| 48 h & close out |  |  |  |  |  |

- **Sample Size:**

The aim of this study is to compare the ability of antibiotic paste versus calcium hydroxide used as intra-canal medication in reducing pain and level of endotoxins in necrotic teeth with apical periodontitis. Based on previous study by Ehrmann, et al. (2003), a medium effect size of approximately 0.25 is expected. A total sample size of 24 patients will be sufficient to detect an effect size of 0.25, a power of 80%, and a significance level of 5%. This number has been increased to a total sample size of 28, to adjust for using nonparametric tests. The number is again increased to a total sample size of 36 (18 in each of the two groups) to allow for losses of around 25%. Sample size was calculated using G*Power program (University of Düsseldorf, Düsseldorf, Germany)^[[13]](#footnote-13)^ . minimal clinical difference 3.5 and 4.5 at 24 hrs and 48 hrs respectively.

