# 0 reading represents “no pain”

# 3 readings represent “mild pain”

# 4- 6 readings represent “moderate pain”

# 7- 10 readings represent “severe pain”

Secondary outcomes will be collected by the operator by commercial standard kit then stored at -80^0^ C so that all samples would be processed at the same time by LAL assay for quantification of bacterial endotoxins.

- **Statistical analysis:**

Data will be analyzed using IBM SPSS advanced statistics (Statistical Package for Social Sciences), version 21 (SPSS Inc., Chicago, IL). The level of endotoxins will be described as mean and standard deviation. The level of pain will be described as median and range or interquartile range, as appropriate. The level of endotoxins will be explored for normality using Kolmogrov-Smirnov test and Shapiro-Wilk test. If the exploration of data reveals that the collected values are normally distributed, a 2-way ANOVA with repeated measures will be performed to compare between the 2 groups and the change with time. If the interaction between the groups and time is found to be significant, a 1-way repeated measures ANOVA will be used to examine significant differences between time periods within each of the two groups. The Student’s t-test will be performed to test the significance between the two groups at each time period. If the exploration of data reveals that the level of endotoxins is not normally distributed and for the analyses of the pain score, Mann-Whitney U test will be performed to test the significance between the 2 groups at each time period. Friedman’s test followed by multiple comparisons test will be performed to test the significance between the 4 time periods within each group. In addition, correction of p-value will be done using Bonferroni adjustment to avoid hyperinflation of type 1 error that arises from multiple comparisons. A p-value less than or equal to 0.05 will be considered statistically significant. All tests will be two tailed. The effect size will be measured using standardized mean difference.

- **Data monitoring:**

There will not be a Data Monitoring Committee for the following reasons:

- Interim analysis is not involved in the trial so periodic inspection of the accumulating outcome data is not required.
- Short duration of the trial.
- Minimal risks of the trial.
- **Harms**

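### The between-arm endotoxin comparison uses Student's t-test on a normality check alone; its 5% level drifts only if losses fall unevenly and the arms' SDs also differ at day 7

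*Protocol*

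**What the plan says.** The Protocol's Statistical analysis section sets out two routes for endotoxin. The choice between them rests on shape: "The level of endotoxins will be explored for normality using Kolmogrov-Smirnov test and Shapiro-Wilk test". The parametric route opens with "If the exploration of data reveals that the collected values are normally distributed". It consists of a two-way repeated-measures ANOVA, one-way follow-ups within arms, and, for the comparison between arms, Student's "t-test will be performed to test the significance between the two groups at each time period". If normality is rejected, "Mann-Whitney U test will be performed to test the significance between the 2 groups at each time period". Neither equal spread nor an unequal-variance version of the t-test is mentioned.

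The error rate is fixed in the same section: "A p-value less than or equal to 0.05 will be considered statistically significant" and "All tests will be two tailed". A Bonferroni step is also planned ("correction of p-value will be done using Bonferroni adjustment").

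The Trial Design section gives 1:1 allocation. The Sample Size section sets 36 patients, 18 per arm, after an increase "to allow for losses of around 25" per cent. It does not say how losses would divide between the arms, and the protocol gives no endotoxin SD.

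**The concern.** Student's t-test in its ordinary form rests on two conditions, normality and equal variances. The plan checks the first and has no route for failure of the second: the Mann-Whitney fallback is triggered by non-normality, not by unequal spread.

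Equal arm sizes protect the pooled test, but they are not assured for the comparison that matters most. The third endotoxin sample is taken after 7 days of medication, so a patient who misses the second visit has no post-medication value. If one arm ends up smaller and the SDs differ, the pooled standard error is too small or too large, depending on which arm has the greater spread. The p-value for the day-7 endotoxin comparison would then not carry the stated 5% two-sided level. The Bonferroni step does not help, because it scales a p-value that is already miscalibrated.

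**Working it through.** **Inputs from the protocol.** 36 patients, 18 per arm; losses of around 25%; two-sided test at 0.05.

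**Assumptions.** Normal data, equal means, and SD ratios of 1.5, 2 and 3, because the protocol gives no SD.

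**The plan's own figure.** The base size of 28 inflated for 25% losses is 28/0.75 = 37.3 or 28 × 1.25 = 35, depending on the convention. Both are within 2 of the stated 36. A quarter of 36 is 9, leaving 27.

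**Why arm size matters.** Let the SDs be 1 and 2.
- True variance of the mean difference: s₁²/n₁ + s₂²/n₂.
- Average pooled estimate: [(n₁−1)s₁² + (n₂−1)s₂²]/(n₁+n₂−2) × (1/n₁ + 1/n₂).
- 14/14: true 1/14 + 4/14 = 0.357; pooled (13 + 52)/26 × 2/14 = 0.357. They agree.
- 15/12, SD 2 in the smaller arm: true 1/15 + 4/12 = 0.400; pooled (14 + 44)/25 × 0.15 = 0.348. Too small, so too many rejections.
- 15/12, SD 2 in the larger arm: true 4/15 + 1/12 = 0.350; pooled (56 + 11)/25 × 0.15 = 0.402. Too large, so too few rejections.

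**Actual error rate of Student's test at nominal 5%.** These figures come from numerical integration over the two chi-square variance distributions. Where two are shown, the first has the larger SD in the smaller arm and the second has it in the larger arm.

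| Arms | SD ratio 1.5 | SD ratio 2 | SD ratio 3 |
| --- | --- | --- | --- |
| 18/18 | 5.1% | 5.3% | 5.5% |
| 14/14 | 5.1% | 5.3% | 5.6% |
| 15/12 | 6.2% / 4.2% | 7.1% / 3.9% | 8.1% / 3.8% |
| 16/11 | 6.9% / 3.7% | 8.4% / 3.2% | 10.0% / 2.8% |

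Welch's test stays at 4.9–5.1% in every cell.

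**How likely uneven losses are.** If 9 losses fall at random over 36 patients with 18 per arm, the number lost from one arm is hypergeometric: P(d) = C(18,d)·C(18,9−d)/C(36,9), with C(36,9) = 94,143,280.
- Split of 6:3 or worse (arms 15/12 or worse): 2 × (15,148,224 + 4,869,072 + 787,644 + 48,620)/94,143,280 = 0.44.
- Split of 7:2 or worse (arms 16/11 or worse): 2 × (4,869,072 + 787,644 + 48,620)/94,143,280 = 0.12.

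**Average over all random splits.** Weighting each split's error rate by its probability gives 5.2%, 5.5% and 5.9% at SD ratios 1.5, 2 and 3.

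**Price of Welch when the SDs are equal.** At a true difference giving about 80% power, simulated power is 0.798 (Student) against 0.797 (Welch) at 14/14, and 0.771 against 0.762 at 16/11. The larger loss is 0.771 − 0.762 = 0.009.

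**The case against.** The strongest reply is that Student's t-test is a standard choice for a 1:1 trial with 18 per arm, that the text never says pooled, and that a statistical analysis plan not shown may settle the version. This stands in part. Pooled is the ordinary meaning of the unqualified name, and the protocol does fix a test and the condition for using it. It contains no contradiction, however, and with equal arms the choice does almost no damage.

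A reader might infer that losses of 25% together with unequal SDs are enough to spoil the 5% level. They are not: equal losses leave it at 5.1–5.6%. Nor does the protocol forecast uneven losses, or even 9 losses. The 25% is an allowance, and the step from 28 to 36 covers 8 patients. Averaged over random splits, the drift is under 1 percentage point.

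A second reply is that a paste that changes the spread will probably change the mean too, and then there is no type I error to inflate. This narrows the point: the tabulated rates need equal means with unequal SDs. It does not remove it, because the pooled standard error is mis-sized whatever the true difference in means.

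The scope is also narrow. The first two samples precede the medication, so treatment cannot make their spreads differ. The primary outcome, pain, is compared by Mann-Whitney and is untouched.

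**Conclusion.** The point holds as a minor one. The protocol names a test that assumes equal variances and conditions it on normality alone. The result is close to 5% if the arms stay equal. It departs from 5% only when arm sizes and SDs both differ, in a direction set by whether the smaller or the larger arm is the more variable: about 6–8% or about 4% at 15/12, and about 7–10% or about 3–4% at 16/11. A split of at least 15/12 would not be rare if 9 patients were lost at random (probability 0.44); at least 16/11 would be uncommon (0.12).

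These sizes rest on assumed SD ratios of 1.5 to 3, normal data and 9 losses; the documents support none of the SD ratios. The point concerns a secondary outcome, applies only if normality is accepted, and bears chiefly on the third sample. The documents do not support reading it as a threat to the trial's main conclusion.

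**What to change.** In the Protocol's Statistical analysis section, replace Student's t-test with Welch's (unequal-variance) t-test for the between-group endotoxin comparison. Use it whenever the parametric route is taken, without a preliminary test of variances.

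The change is one phrase in the analysis text and needs no new data, visits or patients. The cost is under 1 percentage point of power when the SDs are in fact equal.

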**1. Setting and location:**

*** Source of patients**: Out patients of the clinic of endodontic at the faculty of oral and dental medicine, Cairo University, Urban area, Cairo governorate.

*** Operator Qualification:** Post Graduate Master’s Degree Student.

*** Dental units**: Adec 200 U.S.A.

* **X-ray machine**: ViVi, S.r.I, Italy.

* **X-ray film**: Intraoral digital sensor.

1. **Eligibility criteria :**
2. *Inclusion criteria:*
   1. Age between 18-55 years old.
   2. Males or Females.
   3. Maxillary or mandibular single rooted premolar teeth with:

- Non-Vital response of pulp tissue.
- Slight widening in lamina dura.
- Tenderness to percussion.
  1. Positive patients’ acceptance for participation in the study.

1. *Exclusion Criteria*:
   1. Pregnant females: Pain degree change may be due to hormonal change, and some medications are contra indicated.
   2. Patients who had received antibiotic treatment during the last 3 months.
   3. Patients having more than one tooth require root canal treatment.
   4. Teeth with:

- Periodontal probing depth > 4mm.

- Could not be isolated with a rubber dam.

- Fluctuant facial swelling (acute abscess)

- Previous root canal treatment.

- **Final Diagnosis:**
- Mandibular or maxillary single rooted premolar teeth with or without pain.
- Tenderness to percussion.
- On using electric pulp tester it gives response of non-vital pulp.
- On radiographic examination it might have slight widening in lamina dura.
- **Intervention:**

Full medical and dental history using a schematic dental chart will be obtained from all patients treated during this study. Each tooth will be evaluated for vitality (sensitivity) of pulp tissues using electric pulp tester

The patients will be randomly divided into 2 groups:

- ***Experimental group***: antibiotic paste intra-canal medication.
- ***Control group:*** calcium hydroxide intra-canal medication.
- **Sequence of Procedural steps:-**

1. Each patient will be given pain scale chart in order to record his /her pain level before any intervention.
2. Tooth will be anaesthetized using nerve block or infiltration technique by local anesthesia^[[1]](#footnote-1)^.
3. Isolation & disinfection:-

Teeth will be isolated with a rubber dam, and disinfection of their external surfaces will be performed by using 30% hydrogen peroxide followed by 2.5% sodium hypochlorite (NaOCl). Subsequently, 5% sodium thiosulfate will be used to inactivate the disinfectant agents.

1. Access:-

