**رقم المريض: ( ) رقم تليفون الطبيب: ( )**

يرجي وضع علامة علي المقياس ادناة لاظهار شدة ألمك.

1. **Patient training (١) تدريب**

[figure not shown]

1. **Preoperative (٢) قبل العلاج**

[figure not shown]

1. **After 6 hours (٣) بعد سته (6) ساعات**

[figure not shown]

**Figure(6):** pain scale chart

1. **After 12 hours (٤) بعد اثنا عشر (١٢) ساعة**

[figure not shown]

1. **After 24 hours (٥) بعد أربع و عشرون (٢٤) ساعة**

[figure not shown]

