**Assessor Chart**

**Patient No.:**

| Examiner Assignment | Score | Date | Follow up by hours |
| --- | --- | --- | --- |
|  |  |  | 6 |
|  |  |  | 12 |
|  |  |  | 24 |
|  |  |  | 48 |

**Figure(8) :** The assessor chart

**
[figure not shown]
**

**Figure(9) :** The informed consent form given to each patient.

[figure not shown]

**Figure(10) :** The informed consent form given to each patient.

1. #### Carpule3M™ ESPE™ Ubistesin™ Articaine HCI 4% & Adrenaline 1:100,000 3M Australia

   [↑](#footnote-ref-1)
2. Dentsply Maillefer, Ballaigues, Switzerland [↑](#footnote-ref-2)
3. Root ZX, J.Morita USA, Irvine, CA. [↑](#footnote-ref-3)
4. Mani, Tochigi, Japan [↑](#footnote-ref-4)
5. **FKG Dentaire SA,switzerland.** [↑](#footnote-ref-5)
6. ^5^X-Smart, DentsplyMaillefer, USA.

   6MD-Chelcream, META BIOMED CO.,LTD, Korea.

   7Household Cleaning Products Of Egypt, 10th Of Ramadan, Egypt [↑](#footnote-ref-6)
7. [↑](#footnote-ref-7)
8. . [↑](#footnote-ref-8)
9. Dentsply Maillefer, Ballaigues, Switzerland [↑](#footnote-ref-9)
10. 3M ESPE, Seefeld, Germany [↑](#footnote-ref-10)
11. **FKG Dentaire SA,switzerland** [↑](#footnote-ref-11)
12. ^4^ADSEAL, META BIOMED CO.,LTD, Korea. [↑](#footnote-ref-12)
13. G*Power program (University of Düsseldorf, Düsseldorf, Germany). Faul, F., Erdfelder, E., Lang, A.-G., & Buchner, A. (2007). G*Power 3: A flexible statistical power analysis program for the social, behavioral, and biomedical sciences. Behavior Research Methods, 39, 175-191. [↑](#footnote-ref-13)

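### Preoperative pain is recorded for every patient, but the between-group pain test makes no use of it, so a valid analysis gives up precision and leaves chance baseline imbalance unadjusted

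*Protocol*

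**What the plan says.** The preoperative score is collected by design, and three places in the protocol agree on this:

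- Sequence of Procedural steps, first step: "Each patient will be given pain scale chart in order to record his /her pain level before any intervention".
- Participant timeline: patients "will record preoperative and postoperative degree of pain at 6, 12, 24 and 48hrs".
- The pain scale chart (Figures 6 and 7) has its own preoperative item, "Preoperative (٢) قبل العلاج", ahead of the four postoperative ones.

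Entry does not fix the starting level. The Final Diagnosis list admits "Mandibular or maxillary single rooted premolar teeth with or without pain".

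The Statistical analysis section then names the tests for pain. Between groups, "for the analyses of the pain score, Mann-Whitney U test will be performed to test the significance between the 2 groups" at each time period. Within groups, Friedman's test is used to "test the significance between the 4 time periods within each group". No change score, covariate-adjusted model or stratified test is mentioned for pain. The assessor chart (Figure 8), under "Follow up by hours", has rows for 6, 12, 24 and 48 hours and none for the preoperative score. The Randomization section describes a computer-generated sequence and mentions no stratification by baseline pain.

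**The concern.** A patient who starts at 7 and one who starts at 0 may well score differently at 6 hours whatever medication is placed. An unadjusted comparison counts that difference as noise. In a small trial without stratification, the groups may also start at different levels by chance, and part of that gap then sits inside the observed treatment difference. A covariate measured before the medication is placed, on the same scale as the primary outcome, is the obvious means of removing both. Here it is collected from everyone but has no stated use. At stake is the precision of the primary comparison, and how far its result can be trusted if the groups turn out to differ at baseline.

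**Working it through.** **Group sizes.** The Sample Size section gives 24 in total, raised to 28 for nonparametric testing and to 36 for losses. The 24 can be reproduced with a repeated-measures ANOVA: f = 0.25, 2 groups, 4 measurements, alpha 0.05 and an assumed within-patient correlation of 0.5. The within-between interaction then has power 0.816 at N = 24. The next steps are 24 × 1.15 = 27.6, so 28, and 28 × 1.25 = 35, so 36 when made even. At 1:1 allocation this means 14 per group after losses and 18 per group as recruited. The between-group factor of the same ANOVA would need 82, so the between-group comparison has little precision to spare.

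**Is the baseline in any pain analysis?** Pain has five readings: preoperative, 6, 12, 24 and 48 hours. Endotoxin has three samples. The four periods of the Friedman test therefore match only the postoperative pain readings. Reading the Mann-Whitney clause to include a preoperative comparison would test the baseline, not adjust for it.

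**Chance imbalance.** The SD of the baseline difference, in units of the patient-level SD, is √(2/n).

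- n = 14: √(2/14) = 0.378. P(|difference| > 0.5 SD) = P(|Z| > 0.5/0.378 = 1.32) = 18.6%.
- n = 18: √(2/18) = 0.333. P(|Z| > 0.5/0.333 = 1.5) = 13.4%.

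**In NRS points.** The protocol gives no preoperative SD, so I assume 2 to 3 points. With r = 0.5 and equal SDs before and after, half of a baseline difference is expected to carry into the outcome.

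| Per group | One SE of baseline difference | Carried over at one SE | 95% limit (1.96 SE) | Carried over at 95% limit |
|---|---|---|---|---|
| 14 | 0.76 to 1.13 | 0.38 to 0.57 | 1.48 to 2.22 | 0.74 to 1.11 |
| 18 | 0.67 to 1.00 | 0.33 to 0.50 | 1.31 to 1.96 | 0.65 to 0.98 |

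**Gain from adjustment.** Residual variance is multiplied by 1 − r², and the equivalent group size is n/(1 − r²). r is assumed.

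| r | 1 − r² | 14 per group is worth | 18 per group is worth | Unadjusted power of 80% becomes |
|---|---|---|---|---|
| 0.3 | 0.91 | 15.4 | 19.8 | 83% |
| 0.5 | 0.75 | 18.7 | 24.0 | 90% |
| 0.7 | 0.51 | 27.5 | 35.3 | 97.5% |

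These are normal-theory figures. A simulation of the actual choice compared the Mann-Whitney test with rank ANCOVA. It used scores rounded and limited to 0-10, an SD of 2.5, a true shift of 1 SD, alpha 0.05 and 3,000 runs per setting:

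| r | 14 per group: Mann-Whitney / rank ANCOVA | 18 per group: Mann-Whitney / rank ANCOVA |
|---|---|---|
| 0 | 0.65 / 0.66 | 0.77 / 0.77 |
| 0.3 | 0.65 / 0.68 | 0.79 / 0.81 |
| 0.5 | 0.65 / 0.75 | 0.77 / 0.85 |
| 0.7 | 0.67 / 0.86 | 0.78 / 0.95 |

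With no true difference, rejection rates were 0.039 to 0.050 for Mann-Whitney and 0.043 to 0.054 for rank ANCOVA.

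**The case against.** The strongest reply is that nothing here is invalid. Under randomization the Mann-Whitney p-value already allows for chance imbalance, and the simulation bears this out. That stands. A reader might infer that the primary comparison is biased or has an inflated false-positive rate; the protocol does not support that reading.

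Second, the imbalance may matter little. The only NRS benchmarks in the protocol are minimal clinical differences of 3.5 points at 24 hours and 4.5 at 48 hours. Even the extreme carry-over at 14 per group is 0.74/4.5 = 16% to 1.11/3.5 = 32% of these, and a typical one is about half as large. This also stands, and it limits the weight of the imbalance argument. It does not touch the precision argument.

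Third, r may be low. Anaesthesia, instrumentation and medication come between the baseline and the first reading. The outcomes table text counts hours from obturation, whereas the procedural steps place the readings before the seven-day visit; under the former, the baseline would be at least a week old. At r = 0.3 the gain is slight. The documents cannot settle this.

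Fourth, a reader might infer from Figure 8 that the preoperative score is discarded. That goes too far: the patient's pain chart is itself an outcome collection form, carries the preoperative item and is returned to the operator. The Friedman sentence also covers non-normal endotoxin data, so its count of four is loose evidence. What can be said is that the score has no stated role.

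Finally, covariate adjustment might be left to a separate analysis plan. But the protocol itself names the pain test, so this is a choice it makes rather than a detail it defers.

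**Conclusion.** The point holds as a matter of efficiency and of robustness to chance imbalance, not of validity. The preoperative NRS is available for all patients, is taken before the medication is placed, and is not used in the stated between-group analysis. The imbalance probabilities of about 19% and 13% follow from the group sizes alone. The gain rests on an assumed correlation: small at 0.3, substantial at 0.5 or more, and effectively no loss at 0. The figures in NRS points rest further on an assumed SD of 2 to 3 and on equal SDs before and after. That baseline pain really varies widely is not established either: entry with or without pain permits it, but every tooth must be tender to percussion and no SD is given. The change is worth making because it costs almost nothing and the comparison is small. It is not a condition for the trial to be interpretable.

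**What to change.** In the Statistical analysis section, make the between-group comparison of postoperative NRS at each time point a rank ANCOVA: rank the preoperative and postoperative scores over all patients, fit the postoperative rank on treatment group and preoperative rank, and test the group term. Apply the Bonferroni correction as for the planned tests. Keep the unadjusted Mann-Whitney test as a sensitivity analysis. Add a preoperative row to the assessor chart (Figure 8), so that the baseline score travels with the outcome data. Write this down before any data are examined; otherwise a decision to adjust could follow from a visible imbalance.

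The cost is one degree of freedom, slightly more analysis work and one line on a form. No new data, visits or patients are needed.

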**O: outcomes:**

|  | **Outcome measure** | **Tool for measurement** | **Unit of measurement** |
| --- | --- | --- | --- |
| Primary | Postoperative Pain | Numerical rating scale (Brunelli et al, 2010) | Ordinal |
| Secondary | Quantification of endotoxins | LAL assay | EU/mL |

Postoperative pain will be measured using Numerical Rating Scale (NRS) after 6, 12, 24 and 48 hours from the end of root canal obturation **(Evaristo et al. 2013)**

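### The fixed Bonferroni correction is valid, but Holm's step-down version would keep the same 5% family-wise limit and never reject less: a low-severity, nearly free improvement

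*Protocol*

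**What the plan says.** All of the analysis text is in the protocol's Statistical analysis section. For pain, a "Mann-Whitney U test will be performed to test the significance between the 2 groups at each time period". Within groups, "Friedman’s test followed by multiple comparisons test will be performed to test the significance between the 4 time periods within each group". The next sentence sets the correction: "correction of p-value will be done using Bonferroni adjustment to avoid hyperinflation of type 1 error that arises from multiple comparisons". The level and sidedness follow: "A p-value less than or equal to 0.05 will be considered statistically significant" and "All tests will be two tailed". The section also plans descriptive summaries and a standardized mean difference. It mentions no confidence intervals.

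The outcomes table and its note give four postoperative pain readings: "Postoperative pain will be measured using Numerical Rating Scale (NRS) after 6, 12, 24 and 48 hours".

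The Sample Size section starts from 24 patients, raises this to 28 for nonparametric testing, and then to 36 (18 per group) for losses. It names differences of 3.5 at 24 hours and 4.5 at 48 hours as clinically minimal.

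The section does not say which comparisons form the family to which Bonferroni applies.

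**The concern.** Single-step Bonferroni holds every p-value in a family of m tests to 0.05/m. Holm's rule holds only the smallest p-value to that threshold and relaxes it for each later one. Both control the family-wise error at 5% whatever the dependence between tests. Where a plan reports only tests and adjusted p-values, Bonferroni therefore has no compensating advantage.

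The trial is small, and it asks its pain question separately at several readings. If the correction is applied to those between-group tests, a true difference present at more than one reading could be reported as non-significant at some of them when Holm would have declared it. What is at stake is the description of how long a benefit lasts, not whether any benefit is found.

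**Working it through.** **Inputs from the protocol.** Four pain readings; two-sided tests; 5% level; Bonferroni; 28 patients before the allowance for losses, so 28/2 = 14 per arm; 36/2 = 18 per arm enrolled.

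**Inputs assumed, because the protocol does not give them.** Pain SD 2.5; within-patient correlation 0.5 (0.7 as a variant); control means 4.5, 4, 3 and 2 at the four readings; scores rounded and clipped to 0-10.

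**The plan's own figure.** The base total of 24 reproduces as a repeated-measures F test of time, or of group by time, with f = 0.25, two groups, four readings, assumed correlation 0.5 and sphericity. The noncentrality is f² × N × m/(1 − ρ) = 0.0625 × 24 × 4/0.5 = 12, on 3 and 66 degrees of freedom, and the power is 0.816. That calculation uses an unadjusted 5%, so it does not help to choose between the two corrections.

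**Thresholds.**
- Four between-group tests, Bonferroni: 0.05/4 = 0.0125 for each.
- Four between-group tests, Holm, on ordered p-values: 0.05/4 = 0.0125, 0.05/3 = 0.0167, 0.05/2 = 0.025, 0.05/1 = 0.05, stopping at the first failure.
- Six within-group pairs (4 × 3/2 = 6), Bonferroni: 0.05/6 = 0.0083 for each. Holm starts at 0.0083 and relaxes to 0.05.

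**What follows without simulation.** Every Holm threshold is at least 0.05/m, so any p-value that passes Bonferroni also passes Holm. The first thresholds are equal, so the chance of at least one rejection is identical.

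**Size of the gain if the family is the four Mann-Whitney tests** (simulation, 14 per arm, correlation 0.5):

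| Assumed true difference | Power per reading, Bonferroni | Power per reading, Holm |
|---|---|---|
| 3.5 points at 24 and 48 h only | 0.75 / 0.69 | 0.77 / 0.72 |
| 3.5 points at 24 h and 4.5 at 48 h only | 0.737 / 0.874 | 0.767 / 0.892 |
| 3 points at all four readings | about 0.60 (average) | about 0.71 (average) |

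A separate simulation with normal data and t-tests (14 per arm, correlation 0.5, 200,000 trials) shows the same pattern. Power per true effect goes from about 0.50 to 0.59 with a standardized difference of 1 at all four readings, from 0.496 to 0.519 with it at two, from 0.496 to 0.497 with it at one, and from 0.105 to 0.125 with a difference of 0.5 at all four. The chance of at least one rejection was the same under both procedures in every scenario, for example 0.806 and 0.806 with a difference of 1 at all four readings.

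**Error control.** With no true difference, the family-wise error is identical for both procedures. In the rank-test simulation it was 3.6% at correlation 0.5 and 3.2% at 0.7; in the t-test simulation it was 4.3%. When true effects exist at 24 and 48 hours only, false rejections at 6 and 12 hours rise from about 1% each under Bonferroni to about 2% each under Holm. This is still within the 5% family-wise limit.

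**The case against.** The strongest reply is that nothing here is wrong. Bonferroni is valid, prespecified and achieves its stated aim, and no other part of the protocol contradicts it. That stands. It rules out calling this an error, and leaves an efficiency improvement.

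The second reply concerns the family. The correction sentence comes directly after the one on Friedman's test and its multiple comparisons, so it may cover only the within-group pairs. In that case the between-group tests are uncorrected and Holm changes nothing for them. This also stands, and it makes the between-group gain conditional. The dominance result itself holds for whichever family is meant.

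The third is that Bonferroni has simple matching simultaneous confidence intervals and Holm does not. That is a real property, but the protocol plans no intervals. A separate analysis plan, not at hand, might.

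Three stronger readings are tempting and are not supported:
- *That the trial loses much of its power.* In the simulation with 3 points at all four readings, the chance of declaring all four differences was 27% with Bonferroni and 51% with Holm. That contrast needs a large assumed effect throughout, and significance at all four readings is a success criterion that the protocol never sets. Its named clinical differences are at 24 and 48 hours only, where the gain is 2 to 3 points per reading.
- *That power is given away at no cost whatever.* Holm has the small costs listed under the fix.
- *That exactly 28 patients will be analysed.* That is the target before the allowance for losses; 36 are to be enrolled.

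**Conclusion.** The point holds as an optional, low-severity improvement. The protocol fixes a valid procedure that is uniformly dominated, for the tests it plans, by one with the same family-wise guarantee. The dominance is a mathematical fact and rests on no assumption about the data.

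The size of the gain does rest on assumptions: SD 2.5, correlation 0.5, the assumed control means, 14 per arm, and a correction that covers the four between-group pain tests. Under these it is about 2 to 3 percentage points per reading for an effect at 24 and 48 hours only, and about 10 points per reading for a large effect at all four. It is zero for the first rejection in every case. If the correction covers only the comparisons after Friedman's test, the between-group pain results are unaffected and the gain is limited to within-group comparisons. No conclusion of the trial becomes invalid if the text stays as it is.

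**What to change.** In the Statistical analysis section, replace *Bonferroni adjustment* with *Holm (step-down Bonferroni) adjustment*, applied separately within each family of comparisons that the correction covers, and report Holm-adjusted p-values. Keep the 5% family-wise level and the two-sided tests. Make the change before unblinded data are seen, so that it cannot look data-driven. Holm, like Bonferroni, needs a known family, so the same sentence should say which comparisons it covers.

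The cost is small:
- Adjusted p-values must be computed outside the SPSS default, which can be done by hand from the unadjusted ones.
- Simple matching simultaneous intervals are given up, though the protocol plans none.
- False rejections at readings with no true difference can rise slightly when other readings have one, within the 5% family-wise limit.

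No patients, visits or data are added.
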